### Timeline

The entire trial period will last 10 weeks (the treatment period is 6 weeks and the follow-up period will last 4 weeks). Participants will need to stop using drugs related to the treatment of NERD during pre-screening and screening, complete a physical safety examination, and sign an informed consent form. At baseline, participants will need to complete the first assessment and then randomly divided into an intervention group and a control group. During the treatment phase, TCM physicians will instruct the participants on how to take the therapy and then evaluate compliance and outcome indicators after 2, 4, and 6 weeks of treatment. The follow-up period will last 4 weeks after the end of treatment. Details are shown in Table 1.

**Table 1 Tab1:** Timeline of the trial

Study period										
	Screening	Baseline	Treatment						Follow-up	
Outcomes	Week -1	Week 0	Week 1	Week 2	Week 3	Week 4	Week 5	Week 6	Week 8	Week 10
**Screening and enrolment**										
Informed consent form	○									
Eligibility for study	○									
Demographic and clinical details	○									
Physical safety examination	○									
Randomization	○									
**Intervention**										
TCM granules/placebo + PPI step-down		○		○		○				
**Assessment**										
VAS of heartburn and reflux		○	○	○	○	○	○	○	○	○
Major symptoms scale		○	○	○	○	○	○	○	○	○
Minor symptoms scale		○	○	○	○	○	○	○	○	○
TCM syndromes scale		○		○		○		○	○	○
SF-36		○		○		○		○	○	○
PRO for chronic gastrointestinal diseases		○		○		○		○	○	○
SAS		○		○		○		○	○	○
SDS		○		○		○		○	○	○
GERD-HRQL		○		○		○		○	○	○
Compliance			○	○	○	○	○	○		
Cointerventions			○	○	○	○	○	○		
Adverse events			○	○	○	○	○	○		

*VAS* visual analog scale, *TCM* traditional Chinese medicine, *SF-36* the MOS 36-item Short From Health Survey, *PRO* Patient-Reported Outcome, *SAS* Self-Rating Anxiety Scale, *SDS* Self-Rating Depression Scale, *GERD-HRQL* the Gastroesophageal Reflux Disease-Health-Related Quality-Of-Life

### Sample size estimation

According to the preliminary trial results from the team and to literature reports, the average effective rate of traditional Chinese medicine treatment for NERD is 90% [25]. The literature reports that the effective rate of PPIs in the treatment of NERD is between 50 and 90% [4, 26], so we used an average of 70%. The trial intends to conduct a superiority test of two independent sample proportions, using a margin of 0.02, an alpha risk of 0.05, and a beta risk of 0.20, assuming an attrition rate of approximately 20%. The estimated sample size is *N* = 174, including 87 cases in the intervention group and 87 cases in the placebo group.

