Due to insufficient patient-response-to treatments and various undesirable negative side effects, more and more scientific researchers in the medical area have begun to consider PPI step-down therapy in recent years. PPI step-down therapy means gradually reducing dosage and patients’ dependence on PPIs according to the outcome and symptoms changes of patients. Multiple strategies may be used to de-escalate (i.e., stop or reduce) PPIs, including abrupt PPI withdrawal, step down therapy, and H_2_ blocker (i.e., famotidine) substitution. However, one randomized controlled trial (RCT) study showed that about 68% patients experienced symptom recurrence after discontinuation of long-term PPI therapy [18], thus, meaning that stopping PPIs is not sufficient to control patients’ symptoms in a long-term period.

The use of complementary and alternative approaches has proven to have an effect on the treatment of NERD [19, 20]. In recent years, numerous studies have evaluated the clinical effectiveness of traditional Chinese Medicine (TCM) herbals for the treatment of NERD. A review article showed that in addition to their acid-suppressive properties, anti-inflammatory, and antioxidant activity of the herbal remedies, these herbal medicine seem to provide a safer and more effective treatment compared to their pharmaceutical drug counterparts. Herbal remedies used in human studies have led to the alleviation of heartburn and regurgitation related to NERD where PPI treatment has failed to show a promising effect. Moreover, herbal remedies appeared to have a longer-lasting therapeutic effect than conventional anti-secretory agents have [19]. A systematic review has reported that the total effective rate of TCM alone was superior to single PPIs or prokinetics for their clinical efficacy. TCM also has advantages in reducing recurrence rate and adverse events like constipation, faint headache experience, and nausea [21]. Although TCM has been examined for its ability to alleviate PPI-refractory symptoms, including the reduction of recurrence of these symptoms as well as improve the quality of life of patients, a high-level evidence-based support and thorough understanding of the underlying mechanisms of the action of TCM herbal remedies were lacking [22].

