### Statistical analysis

This trial will use intention-to-treat (ITT) analysis as the main method to evaluate the outcome results. To deal with missing outcome variables that remain to be recorded, the last record data will be carried over to the end or a multiple imputation method will be used.

Statistical analysis will be conducted using the SPSS 21.0 software. The significance level is established at 0.05, and the limits of the confidence interval are 95%. Descriptive analysis and categorical variables will be described in frequency tables and as percentages or composition ratios; continuous variables will be described in terms of means and standard deviations (SDs), or medians, lower quartiles (P25), upper quartiles (P75), minimum values, and maximum values. Comparative analyses between two groups will be performed for categorical variables using the chi-squared test, Fisher’s exact probability method, the Wilcoxon rank-sum test, or the CMH test. Continuous variables that conform to a normal distribution will be compares using a *t*-test (for homogeneity of variance between groups, with 0.05 as the test level; if the variance is heterogeneous, the Welch-Satterthwaite *t*-test will be used), while those that conform to a non-normal distribution will be compared using the Wilcoxon rank-sum test or the Wilcoxon signed-rank test. Hypothesis testing will use the two-sided test uniformly, and *P* ≤ 0.05 will be considered statistically significant.

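### The 87 per arm does not follow from the stated inputs for a two-sided test against the 0.02 margin, the listed tests never use that margin, and the 70% control rate does not describe the control arm

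*Protocol article*

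**What the plan says.** Under Sample size estimation, the protocol article takes the treatment rate from the team's preliminary results and the literature: "the average effective rate of traditional Chinese medicine treatment for NERD is 90"%. For control it cites a range: "The literature reports that the effective rate of PPIs in the treatment of NERD is between 50 and 90"%. From that range it takes the midpoint: "so we used an average of 70"%. The design of the calculation is described in these words: "The trial intends to conduct a superiority test of two independent sample proportions". The remaining planning values follow in the same sentence: "using a margin of 0.02, an alpha risk of 0.05, and a beta risk of 0.20, assuming an attrition rate of approximately 20"%. The result is 174 patients, 87 per arm. The section gives no formula, no sidedness and no account of how attrition entered.

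Under Statistical analysis, "Hypothesis testing will use the two-sided test uniformly". The tests listed for categorical outcomes are chi-squared, Fisher's exact, Wilcoxon rank-sum and CMH. No margin and no confidence-limit criterion appears. The main analysis is by intention to treat, with last observation carried forward or multiple imputation for missing outcomes.

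The inclusion criteria require more than 8 weeks of PPI treatment with an unsatisfactory result. The control arm receives placebo granules with the same step-down as the intervention arm: half-dose PPI in weeks 1–2, famotidine in weeks 3–4, no acid suppression in weeks 5–6. Under Primary outcomes, a responder has a weekly VAS reduction of at least 50% from baseline in at least half of the 6 weeks.

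**The concern.** Three parts of the sample-size basis do not fit the rest of the article.

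- **Attrition.** The stated total looks like an evaluable number multiplied by 1.2. Losing 20% calls for division by 0.8, which gives a larger number.
- **Margin.** The size is computed for superiority by more than 0.02, but every listed test has a null hypothesis of zero difference. A significant result would support a weaker claim than the one the trial was sized for.
- **Control rate.** The 70% is the midpoint of a wide range for NERD patients on PPIs. The control arm consists of patients in whom PPIs did not work well enough, and acid suppression is reduced and then withdrawn. The article does not tie its effective rate to the trial's own responder rule.

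At stake is how the stated power will be read. If the trial is neutral, readers will weigh that result by an 80% figure that belongs to a different test and a different population.

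**Working it through.** **Inputs.** From Sample size estimation: p1 = 0.90, p2 = 0.70, margin δ = 0.02, alpha 0.05, power 0.80, attrition about 20%, 87 per arm. From Statistical analysis: two-sided testing, so z = 1.96 and 0.8416.

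**Reproducing 87.** The unpooled margin formula is

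n = (z_α + z_β)² × [p1(1−p1) + p2(1−p2)] / (p1 − p2 − δ)²

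= (1.96 + 0.8416)² × (0.09 + 0.21) / 0.18² = 72.67 evaluable per arm.

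- Multiplied by 1.2: 72.67 × 1.2 = 87.2, the stated 87.
- Divided by 0.8: 72.67/0.8 = 90.8, so 91; or 73/0.8 = 91.25, so 92.

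Other two-sided margin formulas divided by 0.8 give 95 (Farrington-Manning), 97 (pooled), 105 (unpooled, continuity-corrected) and 109 (pooled, continuity-corrected). None gives 87.

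**Power at the stated rates.** Power = Φ[(p1 − p2 − δ)/√(0.30/n) − 1.96]. A 20% loss leaves 87 × 0.8 = 69.6 per arm.

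| Analysed per arm | Test against 0.02 | Test of no difference |
|---|---|---|
| 69.6 | Φ(0.18/0.0657 − 1.96) = 78.3% | Φ(0.20/0.0657 − 1.96) = 86.1% |
| 87 | 86.5% | 92.6% |

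Exact enumeration of the chi-squared test gives 86.2% at 70 per arm; the pooled normal approximation gives about 85%. Without the margin, the same unpooled formula needs 0.30 × 7.849/0.20² = 58.9, or 59 evaluable, and 59/0.8 = 73.75, or 74 enrolled. So 87 is more than enough for that test.

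**What the missing margin changes.** If the true difference were exactly 0.02, the margin test would declare superiority in 2.5% of trials. The margin-free test does so more often. For example, at 72% versus 70% with 69.6 per arm, the standard error is √(0.4116/69.6) = 0.077 and Φ(0.02/0.077 − 1.96) is about 4.5%. For control rates of 30–70% and 69.6 to 87 per arm the figure is about 4.2–4.8%.

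**Sensitivity to the rates.** The documents give no responder rates for this population, so the alternatives below are assumptions. Power at 69.6 per arm:

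| Treatment/control | Test against 0.02 | Test of no difference |
|---|---|---|
| 90/60 | 98% | 99% |
| 90/70 (plan) | 78% | 86% |
| 80/60 | 66% | 75% |
| 60/40 | 58% | 67% |

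If only the control rate falls, power rises. If both rates fall towards 50% with the same gap, power falls.

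**The case against.** A reader might infer that the trial fails to reach 80% power. The documents do not support that. The 78% needs both the margin test and an analysis of completers only. The article lists tests without a margin and makes intention to treat with imputation the main analysis. At 90% versus 70%, the chi-squared test exceeds 80% even after 20% loss, and with all 87 analysed both tests exceed it. Imputation may dilute the effect, but complete loss of 20% is already covered by the 69.6 row. The attrition and margin points also pull against each other: the shortfall exists only if the margin is tested.

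A reader might also take the 1.2 multiplication as established. It is an inference. A two-sided, margin-free, continuity-corrected calculation gives 69, and 69/0.8 = 86.25, which rounds up to 87. A one-sided 0.05 margin test with continuity correction, divided by 0.8, gives 85 or 89. The first drops the stated margin; the second departs from the two-sided rule. The 1.2 route remains the simplest that keeps every stated input.

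Nor should the Background statement that "about 68% patients experienced symptom recurrence after discontinuation of long-term PPI therapy" be turned into a control response rate. It concerns recurrence after stopping long-term therapy. The trial's responder rule can be met in weeks 1–4, before acid suppression is fully withdrawn. What the cited literature meant by effective rate cannot be judged from the article either; only the missing link to the responder rule can.

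What stands is that the margin is planned and not tested, the 87 does not follow as a two-sided margin test with proper allowance for loss, and the control rate describes other patients on another regimen.

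**Conclusion.** The point holds as a fault of consistency and justification, not as a demonstrated lack of power. Under the stated inputs, two-sided testing and the unpooled margin formula, 20% loss requires 91–92 per arm rather than 87, and 87 gives about 78% power among completers, a shortfall of under 2 points (3–4 points with pooled variance). The listed chi-squared test has about 86% power under the same loss and rates. The mismatch between planned and tested hypothesis needs no assumption; it follows from setting the two sections side by side. The mismatch of the control rate is equally plain, but its direction and size for power cannot be settled from the documents: over the assumed rates, margin-free power at 69.6 per arm runs from 67% to 99%. This should be corrected, but it does not call the size of the trial into question.

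**What to change.** 1. Make planning and analysis test the same hypothesis. Either drop the 0.02 margin and restate power for the two-sided chi-squared test (about 86% at 90% versus 70% with 69.6 per arm), or keep the margin, require the lower 95% confidence limit of the difference to exceed 0.02, and restate power as about 78% after 20% loss.
2. State the formula and sidedness, and apply attrition by dividing by 0.8. If the margin is kept, say that 80% power after 20% loss would have needed 91–92 per arm.
3. Present the power as conditional on 90% versus 70%. Define both rates by the trial's VAS responder rule in patients with unsatisfactory PPI response under step-down, and give a sensitivity range that varies each rate separately as well as both together.

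The cost is rewording of two sections, with no change in enrolment. Dropping the margin raises the stated power; keeping it lowers the figure slightly.

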### Randomization and blinding

In this trial, center stratification will be used; each center will use the block randomization method, and qualified participants will be divided into intervention and control groups in a 1:1 ratio for grouping. Sequence generation is as follows: a table of random sampling numbers will be completed by an independent statistician through the PROC PLAN procedure in the Strategic Applications Software (SAS) V.9.2, and the results of the random allocation will be published through the network central random allocation system. The statistician will place the groups to be assigned into a double-layered, opaque envelope in sequence and seal the envelopes, and the clinical research coordinator will number the envelopes sequentially and maintain them. Allocation concealment mechanism is as follows: the person who generates the random sequence and decides on the allocation sequence should not be involved in the inclusion of participates and should not be involved in subsequent trials, especially in the measurement of outcomes. Prepare a list of assignment sequences, with each column containing the subject’s serial number, random number, drug name, or group identification. It is important that the serial number of each included subject corresponds to the random number generated in this order and that the order is not changed. Determine the group based on the random numbers. The participants’ sequence number and corresponding grouping will comprise the first-level blind code and, the medicine code will comprise the second-level blind code; each patient’s medicine code will be randomly assigned. Implementation is as follows: the designer, pharmacy, or statistician will each be provided with a copy of the distribution schedule, each sealed in an opaque envelope and kept under lock and key. The placebo used in the control group is treated to look, smell, and even taste similar to the drugs in the treatment group, making it difficult to distinguish. Participants, drug distribution center staff, and trial personnel were unable to determine the type of drug based on its appearance. Each participant will receive the corresponding medication according to their random code. All operations will be completed according to the established SOP guidelines. All codes will be kept in the Good Clinical Practice (GCP) Centre of Xiyuan Hospital. The TCM practitioners and statisticians administering the treatment will be blinded to the grouping.

In the case of serious adverse events or complications in the clinical trials, blinding should be unsealed urgently, and cases of unblinding should be treated as dropout participates.

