### Study setting

This multicenter, double-blind, RCT will be conducted at six hospitals in China (Xiyuan Hospital of China Academy of Chinese Medical Sciences; Guangdong Provincial Hospital of Traditional Chinese Medicine; Wuhan No.1 Hospital; The First Affiliated Hospital of Tianjin University of Traditional Chinese Medicine; Traditional Chinese Medicine Hospital of Kunshan; Liuzhou Hospital of Traditional Chinese Medicine). These six hospitals are all qualified to conduct clinical studies and relevant experience. A total of 174 participants will be recruited from the hospital outpatient departments, hospital websites, and posters. Participants will be divided into three groups according to their different TCM syndromes, and those with the same syndrome will be divided into the intervention group and the control group at a 1:1 ratio.

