#### Intervention group

Based on the curative effect of treating NERD in clinical practice, we selected three kinds of TCM granules based on TJ methodology. According to the different TCM syndromes, participants with stagnation of liver and stomach-heat syndrome will be treated with Tongjiang (TJ) granule, those with spleen deficiency and dampness-heat syndrome will be treated with Jianpiqinghua (JQ) granule, and those with intermingled heat and cold syndrome will be treated with Wenpiqingwei (WQ) granule. These herbal granules are available from the Xiyuan Hospital as an in-hospital preparation. TCM granules are concentrated herbal particles obtained by the mean of spray drying the hot water extract of a mixture of raw herbs. TCM granules are extracted with water to make an aqueous extract or decoction used for treatment. Each bag of granules (approximately 20 g) will be dissolved in 200 ml water and taken twice a day, 1 h after meal. Participants in all three groups cooperated with PPI step-down therapy. From week 1 to week 2 of treatment, the dose of PPIs will be half of the original dose, once a day, taken before bedtime. The PPIs will be replaced with famotidine 20 mg from week 3 to week 4, taken before bedtime. From week 5 to week 6, acid-suppressive drugs will be withdrawn, and only TCM granules will be administered. There will be 6 weeks of treatment and 4 weeks of follow-up.

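### Allocation strata (TCM syndrome in one section, centre in another) and the timing of randomisation are not reconciled, and the stated tests fix no adjustment for centre, syndrome or baseline VAS

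*Protocol article*

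**What the plan says.** **Allocation factor.** The Study setting section sorts participants by TCM syndrome into three sets; it then adds that "those with the same syndrome will be divided into the intervention group and the control group at a 1:1 ratio". Under Randomization and blinding, "center stratification will be used; each center will use the block randomization method", also at 1:1; syndrome is not mentioned there. The trial "will be conducted at six hospitals in China". The Intervention group section states that "we selected three kinds of TCM granules based on TJ methodology", one for each syndrome, and the Control group section gives the matching placebo.

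**Timing.** The Timeline text says: "At baseline, participants will need to complete the first assessment and then randomly divided into an intervention group and a control group". Table 1 marks randomisation in the Week -1 screening column, together with consent and eligibility. The first VAS and symptom assessments are marked at Week 0.

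**Analysis.** The Statistical analysis section says: "Continuous variables that conform to a normal distribution will be compares using a" *t*-test, with the Welch version for unequal variances and Wilcoxon tests for non-normal data. Categorical outcomes are to be compared "using the chi-squared test, Fisher’s exact probability method, the Wilcoxon rank-sum test, or the CMH test". No stratum, covariate or model is named. Under Primary outcomes, baseline enters in two ways: the responder rule needs a 50% or greater fall in weekly VAS from baseline, and the change in VAS is compared between arms.

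**The concern.** Syndrome fixes the product and also describes a type of patient, so balance within syndrome matters for reading the result. The article promises that balance in one section and describes a scheme in another that need not deliver it. A reader cannot tell whether there are 3, 6 or 18 strata, and so cannot tell which factors the analysis should reflect.

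The timing conflict bears on the endpoints. Both VAS endpoints are measured against baseline, so it should be clear that baseline was recorded before allocation.

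The tests named do not use the factors that shaped the allocation, nor baseline as a covariate. Precision is given up, and any chance imbalance stays in the estimate uncorrected.

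**Working it through.** **1. The plan's own figure.** The sample size section uses rates of 90% and 70%, a margin of 0.02, alpha 0.05 (two-sided in the Statistical analysis section), beta 0.20 and 20% attrition. One route that reaches the stated total, with unpooled variance, is:

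n = (1.960 + 0.842)² × (0.9×0.1 + 0.7×0.3) / (0.20 − 0.02)² = 72.7 per arm; 72.7 × 1.2 = 87.2, so 87 per arm and 174 in all.

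Other routes land close by. What matters here is that the trial is sized on a proportion, not on mean VAS change.

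**2. How different the schemes are.**
- Centre only: 174/6 = 29 per stratum.
- Syndrome only: 174/3 = 58 per stratum.
- Both: 174/18 = 9.7 per stratum.

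**3. Imbalance within one syndrome if only centre was used.** Assumptions: one third of participants have the syndrome, independently of centre. Blocks hold the overall split near 87:87, so the arm difference D within the syndrome has approximately

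Var(D) = 174 × (1/3) × (2/3) = 38.7, SD = 6.2.

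With 58 participants D is even, so with a continuity correction P(|D| ≥ 10) = P(|Z| ≥ 9/6.2), about 0.15. A difference of 10 is a 34:24 split. Simulation with 6 centres of 29 and assumed block sizes of 4, 6 and 8 gave SD 6.2–6.3 and about 15%. For a syndrome share of 0.2 the SD is √(174×0.2×0.8) = 5.3; for 0.5 it is √(174×0.5×0.5) = 6.6. Clustering of syndromes by centre would lower these values.

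**4. Cost of leaving centre out of the analysis.** Simulation with 6 centres of 29, blocks of 4 and assumed centre effects (the article gives none):

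| Continuous outcome, centre ICC | 0 | 0.05 | 0.10 | 0.20 |
|---|---|---|---|---|
| Type I error, unadjusted t | 0.047 | 0.047 | 0.045 | 0.030 |
| Type I error, centre-adjusted | 0.048 | 0.051 | 0.054 | 0.049 |
| Power at 0.43 SD, unadjusted | 0.80 | 0.80 | 0.83 | 0.83 |
| Power at 0.43 SD, adjusted | 0.80 | 0.81 | 0.85 | 0.88 |

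| Binary outcome, between-centre logit SD | 0 | 0.5 | 1.0 |
|---|---|---|---|
| Type I error, chi-squared | 0.054 | 0.047 | 0.037 |
| Type I error, CMH | 0.054 | 0.052 | 0.051 |
| Power at OR 2.5, chi-squared | 0.69 | 0.66 | 0.61 |
| Power at OR 2.5, CMH | 0.69 | 0.68 | 0.65 |

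In the continuous case, mean bias was about zero with or without adjustment.

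**5. Cost of leaving baseline out as a covariate, VAS change only.** With equal variances σ² at both times and baseline correlation r, the change score has variance 2σ²(1 − r) and ANCOVA has σ²(1 − r²). The ratio is (1 + r)/2. At r = 0.3 it is 0.65 and at r = 0.6 it is 0.80. ANCOVA would therefore match the change-score precision of 174 participants with about 114 (174 × 0.65 = 113.1) to 140 (174 × 0.80 = 139.2).

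**The case against.** The two sections can be read together as blocks within centre and syndrome, since naming centre does not exclude syndrome. That reading is possible, but the article never states it. So the passages are unreconciled; it is not proven that they describe incompatible schemes.

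A reader might infer confounding between product and treatment effect. The documents do not support this. Allocation is random under either description, controls receive the matching placebo, and unadjusted tests remain valid, erring on the conservative side as centre effects grow. Only chance imbalance can arise. Its size should not be taken from simple randomisation, which would give SD √58 = 7.6 and about 24%, because centre blocks constrain the split.

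A reader might also say that strata and baseline are ignored. That is too strong: CMH is listed, and both VAS endpoints are defined relative to baseline. What is absent is a named stratum and a covariate.

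The ANCOVA gain could be mistaken for a 25–54% larger trial (1/0.80 to 1/0.65). It applies to the continuous VAS change alone and does not carry over to a responder proportion, the kind of endpoint on which the trial is sized.

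Finally, covariates and CMH strata are often left to an analysis plan, and one may exist unseen. That stands for the modelling detail. It does not settle the two descriptions of allocation or the conflict with Table 1, and the article does commit itself to specific two-group tests.

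**Conclusion.** The point holds as a matter of clarity and efficiency, not validity. Two items rest on the text alone: the allocation factors differ between sections without reconciliation, and Table 1 and the Timeline text disagree on when randomisation occurs. The rest is a matter of degree and rests on assumptions that the article does not supply. If only centre was used, a given syndrome has about a 15% chance of an arm difference of 10 or more, assuming equal thirds unrelated to centre. For VAS change, ANCOVA would cut the variance to 65–80% of the change-score value, assuming r of 0.3–0.6 and equal variances. For the responder rate, stratifying by centre gains 0 to about 4 power points under the assumed centre effects.

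**What to change.** 1. In Study setting and in Randomization and blinding, state the one set of strata actually used: centre, syndrome or both. Recruitment began in June 2020, so this is a statement of what was done; no new allocation method is needed.
2. Align Table 1 with the Timeline text so that randomisation follows the Week 0 assessment, after confirming that this is the practice.
3. In Statistical analysis, compare VAS change by ANCOVA with baseline VAS, centre and syndrome. Enter the factors as main effects, because 18 cells would hold only about 10 participants each. Compare the responder rate by CMH or logistic regression with centre and syndrome. If allocation used centre alone, including syndrome still corrects a chance imbalance in it.
4. Fix these choices before unblinding.

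The cost is wording and one table entry. Centre, syndrome and baseline VAS are already collected, and the sample size remains 174.
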